#### Overview

Phase 2 is a randomized controlled trial. The purpose of this phase is to assess the effectiveness of the My Braces app in improving adherence to oral hygiene advice in orthodontic patients. Table 1 is the schedule of enrolment and assessments.

**Table 1 table1:** Schedule of enrolment and assessments (groups A, B, and C will receive different versions of the intervention, the My Braces app).

Characteristic		Screening	Intervention phase		Final visit
		Visit 1	Visit 2	Visit 3	Visit 4
Visit timing		Baseline	3 months	12 months	End of treatment
Window of flexibility for timing of visits		N/A^a^	1 month	2 months	1 month
**Assessment**					
	Informed consent	✓	N/A	N/A	N/A
	Medical history	✓	✓	✓	✓
	Eligibility confirmation	✓	✓	N/A	N/A
	Taking photographs	✓	N/A	N/A	✓
	Type of dental bite and whether teeth were removed	✓	N/A	N/A	N/A
	Randomization	✓	N/A	N/A	N/A
	Bleeding scores	✓	✓	✓	✓
	Plaque scores	✓	✓	✓	✓
	App subjective quality assessment	N/A	✓	N/A	✓
	Adverse events review	✓	✓	✓	✓

^a^N/A: not applicable.

#### Inclusion Criteria

The study will include patients who have been accepted for fixed orthodontic appliance treatment (“train track”–type braces) at the UCLH NHS Foundation Trust EDH but who have not yet commenced treatment. Patients must also be 10-18 years of age (inclusive) at the start of treatment, have a sufficient number of permanent teeth erupted to allow outcome assessment, be familiar with and have daily access to a smartphone or tablet, and be able to read and communicate in English.

#### Exclusion Criteria

Patients with severe hypodontia (developmental absence of teeth) and craniofacial/orthognathic patients will be excluded from this study. These patients require complex multidisciplinary treatment; the information needs for these patients are therefore different, and treatment involves input from specialties other than orthodontics, and this may therefore influence adherence to treatment advice.

Patients with communication difficulties (for example, severe autism or learning difficulties) will also be excluded from the study.

Patients who are aware that a family member or friend is enrolled in the study (phase 1 or phase 2) will be excluded from the study because it is possible that these patients may become aware of details of the app that may not be relevant to the group that they are randomized to.

#### Recruitment

It is anticipated that recruitment will take approximately 18 months. Patients meeting the inclusion criteria and willing to participate in the trial will be randomized to one of the three study groups:

Group A will act as the control group and will be provided with standard treatment information (verbal and written) and access to the basic version 1 of the app with just a toothbrushing timer. The timer is necessary as the health behavior outcome is toothbrushing duration.

Group B will be provided with standard treatment information (verbal and written) and access to version 2 of the app, which has a toothbrushing timer and provides generic treatment information (a combination of images and text).

Group C will be provided with standard treatment information (verbal and written), and patients will have access to version 3 of the app; this group will have access to the full functionality of the app, which will allow patients to input their own personalized treatment information (including progress photographs), set goals, and develop plans for achieving these goals and will provide the patient and clinicians with appropriate dashboards to monitor progress.

It is important to include Group B, as this will allow the team to ascertain whether it is the personalization of the app content that confers any benefit over and above providing generic information via an app if a difference is found between Groups A and C.

#### Randomization and Allocation Concealment

Randomization will be undertaken using computer-generated random number sequences; block randomization (blocks of 6) will be used to help ensure balance in the allocation of participants to each arm of the trial. Sealed opaque envelopes will be used to ensure allocation concealment. This aspect of the study will be carried out by a member of the research team not involved in recruitment/data collection; this team member will also hold the randomization list and maintain a trial subject enrolment log.

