## Methods

This study will be conducted in 2 phases at the Eastman Dental Hospital (EDH), University College London Hospitals (UCLH) Foundation Trust, London, United Kingdom.

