### Consent Process

A member of the direct care team (the clinician undertaking treatment) will ask eligible patients if they would be prepared to consider involvement in the study. Children younger than 16 years will only be approached if accompanied by a parent/legal guardian. All prospective participants will be provided with patient information leaflets and will be given ample opportunity to ask questions about the study before enrolling. Participants will be required to provide written informed consent to participate in the study. For participants younger than 16 years, parents/legal guardians will also be required to provide written informed consent for their child to participate in this study. Contact details for a designated member of the research team will be provided, and patients will be informed that they may withdraw from the study at any point if they wish to do so. If this happens and participants give a reason for doing so, that reason will be recorded. Withdrawing from the trial will not affect treatment in any way. Signed consent and assent for inclusion will be obtained by a member of the research team. All members of the team have undertaken training in research ethics, including completion of Good Clinical Practice in Secondary Care. Example consent forms can be obtained by contacting the corresponding author.

### Phase 1

Phase 1 is a feasibility study with a convenience sample of patients at different stages of treatment. The purpose of this phase is to assess whether the app is deemed to be of high quality by end users.

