#### Blinding

The outcome assessor will be blinded; however, given the nature of the intervention, it is not possible to blind the patient.

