##### Gingival Bleeding

An estimated clinically relevant difference of 15% and a SD of 20% (standardized difference=0.75) was used, based on advice from [name] (clinical trials coordinator, Restorative Dental Sciences, UCL Eastman Dental Institute, Faculty of Medical Sciences, UCL), who has experience in commercial trials using these outcome measures. The same assumptions were followed as described above, and this indicated a sample size of 38 per group. With the 20% dropout factored in, the sample size calculation is 46 per group (n=138).

Therefore, 138 patients will be recruited. There are a number of assumptions in these calculations; therefore, an internal pilot will be conducted, and the calculations will be repeated using 3-month data for the first 15 patients recruited to each group.

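### One published, fixed block size of 6 lets anyone who knows the earlier allocations in a block deduce up to one allocation in five; random, undisclosed block sizes would remove most of that certainty

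*Protocol article*

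**What the plan says.** The protocol article (Phase 2, Randomization and Allocation Concealment) fixes the method: "block randomization (blocks of 6) will be used to help ensure balance in the allocation of participants to each arm of the trial". It gives no other block size and no random variation of size. Allocation is concealed in sealed opaque envelopes. A team member outside recruitment and data collection handles this part of the trial and keeps both the list and the enrolment log.

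Other sections bear on who might know what:

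- **Methods:** one hospital. "This study will be conducted in 2 phases at the Eastman Dental Hospital (EDH), University College London Hospitals (UCLH) Foundation Trust, London, United Kingdom". No stratification factor is given.
- **Consent Process:** "A member of the direct care team (the clinician undertaking treatment) will ask eligible patients if they would be prepared to consider involvement". A research team member then takes signed consent.
- **Phase 2, Recruitment:** patients "willing to participate in the trial will be randomized to one of the three study groups". For group C only, the app "will provide the patient and clinicians with appropriate dashboards to monitor progress".
- **Blinding:** the outcome assessor is blinded; "given the nature of the intervention, it is not possible to blind the patient". Treating clinicians and recruiters are not mentioned.
- **Data Handling and Confidentiality:** the researchers receive the full set of log-in codes, which are already split into groups A, B and C and are used for assignment. The document linking codes to trial IDs is open to research team members for analysis or unblinding.

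**The concern.** An opaque envelope hides the next card. It does not hide what can be inferred from the cards already opened. With a single known block size and one sequence at one site, anyone who counts from the first enrolment knows where each block ends. If that person also knows the arms given so far in the block, the last place is certain and the one before it sometimes is.

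The stake is selection at entry. Someone who can anticipate the next arm may, even without intending to, bring forward or hold back a patient who seems well or poorly motivated. Motivation drives adherence, which is what the trial measures. Blinding the outcome assessor does not help, because this selection acts before any outcome is scored. Timed brushing, one of the two primary outcomes, is not on the list of baseline measurements, so an imbalance in it could not be adjusted for by its own baseline value. The contrast most exposed is group C against the others, which is the primary hypothesis (full functionality of the app).

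**Working it through.** **Inputs.** Block size 6 (Randomization and Allocation Concealment). Three arms (Phase 2, Recruitment). 46 per group and 138 in total (Sample Size, Gingival Bleeding): "Therefore, 138 patients will be recruited". The 1:1:1 ratio is not stated; it is inferred from the equal group sizes.

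**Consistency with the plan's own figures.** 6 / 3 = 2 per arm per block. 138 / 6 = 23 complete blocks, and 23 × 2 = 46 per arm. The article gives no predictability figure to reproduce.

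**1. Observer who knows the block boundaries and every earlier allocation in the block.** There are 6!/(2!·2!·2!) = 90 equally likely orderings.

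- *Fully determined.* Places 1 to 4: never. Place 5: only if the last two places share an arm, 3 × 4!/(2!·2!) = 18 of 90 = 1/5. Place 6: always. Share = (1/5 + 1)/6 = 20.0%, and 0.20 × 138 = 27.6.
- *At least one arm ruled out.* Places 1 to 6: 0, 0, 0.2, 0.6, 1, 1. Share = 2.8/6 = 46.7%.
- *Best guess correct.* Places 1 to 6: 0.333, 0.400, 0.500, 0.533, 0.600, 1. Mean = 56.1%, against 33.3% by chance.

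**2. Observer who knows the block boundaries but only C versus not-C.** There are 15 arrangements of two C and four not-C.

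- *Certain not C* (both C places used). Places 3 to 6: 1/15, 3/15, 6/15, 10/15. Share = (20/15)/6 = 22.2%.
- *Certain C* (all four not-C places used). Place 5: 1/15; place 6: 5/15. Share = (6/15)/6 = 6.7%.
- C status is known for 22.2% + 6.7% = 28.9%. The exact arm is known for only the 6.7%.

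**3. Partial knowledge.** Assume each earlier allocation is known independently with probability p. The article gives no p, so a range is shown. Full determination needs all four places of the other two arms to be known: 0.20 × p⁴. Known C status is 0.222 × p² + 0.067 × p⁴.

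| p | Fully determined | Of 138 | C status known |
|---|---|---|---|
| 1 | 20% | 27.6 | 28.9% |
| 0.8 | 8.2% | 11.3 | 17.0% |
| 0.5 | 1.25% | 1.7 | 6.0% |

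**4. Effect of varying the block size.** Simulated sequences of 138 with sizes 6, 9 and 12 in random order, and an observer who knows the set of sizes and every earlier allocation but not the order of sizes: fully determined about 2.5%, C status known about 4%, best guess about 53%. A repeat run of 400 simulated trials gave 2.3%, 3.6% and 53%. The same program with a fixed block of 6 returned 20.0%, 28.9% and 56.1%, in agreement with step 1 and with the C-status total in step 2.

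**The case against.** The strongest reply is that 20% describes an observer whom the protocol never creates. The article does not say that recruiters see the running order of allocations, and it gives the list and the enrolment log to someone outside recruitment. Roles are split further: the clinician asks about interest, a researcher takes consent and a third person handles allocation. If several clinicians refer patients (the number is not stated), each may know only their own patients' arms and does not control a patient's place in the sequence.

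Timing also matters. Recruitment is expected to take about 18 months, or 78 weeks, so 78/23 gives one block every 3.4 weeks. The first scheduled follow-up is at 3 months. Nothing shows that a dashboard would reveal the C status of earlier patients in a block before that block closes. Baseline bleeding and plaque are recorded, so gross selection on oral hygiene could be detected, and bleeding is scored by a blinded assessor.

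Most of this stands, and it makes the figures ceilings. A reader might infer that the design itself makes one allocation in five predictable, or that clinicians are unmasked. The article supports neither: it does not give recruiters the earlier allocations, and on clinician masking it is silent, with only the group C dashboards pointing to some access.

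What the reply does not do is close the route. Envelopes and an independent list holder protect unopened assignments only. No section says that those who recruit or take consent are kept from earlier allocations or from the grouped log-in codes.

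**Conclusion.** The point holds as a weakness that is cheap to remove, with medium confidence. A single published block size of 6 at one site, with unblinded patients, lets up to 20% of allocations (about 28 of 138) be fully deduced by someone who knows the block boundaries and all earlier allocations in the block. For someone who knows only C versus not-C, C status is known for up to 29%. These figures rest on an inferred 1:1:1 ratio, one unstratified sequence and complete knowledge. With half the earlier allocations known at random, they fall to about 1% and 6%.

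It would go too far to conclude that allocation will be subverted or that the results will be biased. The figures measure predictability, not an effect on brushing time or bleeding, and the exposure depends on access that the article does not describe.

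**What to change.** In Randomization and Allocation Concealment, replace the fixed size with randomly varying block sizes in multiples of 3, for example 6, 9 and 12 in random order. They should be generated and held only by the independent list holder, with the sizes not disclosed to recruiting or treating staff. Add a sentence that those who approach patients or take consent have no access to earlier allocations or to the A/B/C grouping of log-in codes, and state in Blinding whether treating clinicians are masked.

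The gain is in removing certainty; the best-guess rate improves only slightly, so the access restriction is needed as well. The cost is one line in the randomization program and a few lines of protocol text. An incomplete last block could leave the arms unequal by a few patients: a block of 12 holds 12/3 = 4 per arm, so by at most 4. The article reports that no patient had been recruited when it was published, so at that point no allocation already made would have been affected.

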#### Data Collection

A complete data set will be collected at baseline, 3 months into treatment, 12 months into treatment, and at the end of treatment when the orthodontic appliances have been removed.

Two primary outcome measures have been selected, a health behavior outcome and a clinical outcome, as both are felt to be important. The outcome measures are timed toothbrush use and gingival bleeding scores (these scores indicate the amount of bleeding from the gums, where bleeding is an indicator of inadequate toothbrushing).

The secondary outcomes of interest are as follows: plaque scores, which indicate the amount of plaque on the teeth, where retention of plaque is an indicator of inadequate toothbrushing; number of fixed appliance breakages; number of missed and rescheduled appointments; treatment duration, number of appointments (including emergency appointments for appliance breakages); enamel demineralization (early tooth decay) on the upper anterior six teeth (using standardized photographs), as demineralization is a further indicator of inadequate toothbrushing and nonadherence to the appropriate diet; subjective quality of the app (sections E and F of the uMARS questionnaire); and app engagement.

The following baseline measurements and details will be obtained prior to treatment commencing: age, gender, malocclusion (type of dental bite), whether or not extractions (removal of teeth) are required for treatment, clinical photographs of the teeth (these will be compared with completion of treatment photographs to assess for enamel demineralization), bleeding score, and plaque score.

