## Introduction

### Overview

Orthodontic treatment is a common health care intervention; the most recent National Child Dental Health Survey (England, Wales, and Northern Ireland) indicated that 9% of 12-year-old children are receiving orthodontic treatment, and a further 37% have an unmet need [1]. Treatment duration can be lengthy (2-3 years on average), and adherence to treatment advice is therefore essential for successful outcomes [2]. Failure to adhere to treatment advice can mean that treatment objectives are not met, and there may be detrimental effects on dental health. For example, failing to adhere to dietary advice may result in breakage of the braces and increased overall treatment time, and nonadherence to dietary and oral hygiene advice during treatment can lead to avoidable tooth decay and gum disease.

The National Health Service (NHS) experiences significant costs as a result of nonadherence to treatment [3], and orthodontics is no exception to this. One multicenter study found that 43% of patients failed to complete treatment, and there were no useful predictors for this [4]. To put this into perspective, the NHS England annual expenditure on primary-care orthodontic treatment alone is in excess of £200 million (US $267 million) [5]; noncompletion of treatment therefore represents a significant inefficient use of public resources.

Improving adherence is complex and necessitates a change or modification of existing behavior. A contemporary and widely accepted framework based on multiple models of behavior change developed by Michie et al [6] is the behavior change wheel (BCW). The COM-B model forms the core of the BCW and proposes that individuals need capability (C), opportunity (O), and motivation (M) to perform or adapt a particular behavior (B).

Attempts to improve adherence to treatment advice in orthodontics have included utilizing mind maps and multimedia-assisted methods of providing information. Although these methods have been shown to significantly increase knowledge [7-9], this does not necessarily equate to better adherence to treatment advice or better outcomes [8]. A recent systematic review considered techniques including the use of motivational tests, the Hawthorne effect, and the use of awards and rewards, concluding that there is insufficient evidence to recommend a single method to improve patient adherence to treatment and that more research is required in this area [10].

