### Aims

This study will assess the quality, effectiveness, and acceptability of the My Braces app and test the following primary hypothesis:

Using the full functionality of the My Braces app improves adherence to oral hygiene advice in patients undertaking fixed brace treatment.

The secondary hypothesis is as follows:

Using the full functionality of the My Braces app improves adherence to orthodontic treatment advice (reduction in fixed appliance breakages, missed and rescheduled appointments, treatment duration, number of appointments, and enamel demineralization).

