#### Sample Size

The following assumptions have been made in the sample size calculation:

Data are normally distributed and initial comparison of the 3 groups would use an analysis of variance (ANOVA), followed by 2-sample *t* tests for A versus B, B versus C, and A versus C if any statistical significance is found.

The significance level is *P*<.05 with 80% power.

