##### Timed Toothbrush Use

Using a clinically relevant difference of 20 seconds between groups and a SD of 23.6 seconds from a paper by Tesini and Perlman [21] (standardized difference=0.85) and accounting for multiple testing, 29 patients are required in each group (n=87). Assuming a dropout of 20%, the sample size is 35 per group.

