#### Planned Analyses

Proposed outcome analyses are summarized in Table 2.

For each of the main outcome measures, it is anticipated that regression analysis will be undertaken. The main factor of interest (group allocation) and confounding variables (eg, age, gender, ethnicity) will be entered into univariable regression analyses to determine the level of significance and to limit the number of variables entered into the multivariable analysis. Any factors with *P*≤.10 will be considered for inclusion in the multivariable analysis. Factors with *P*<.05 in the multivariable analysis will be considered as having a significant effect on toothbrushing time or gingival bleeding. Secondary outcomes will be explored in a similar manner.

If necessary, an intention to treat analysis will be performed; all enrolled and randomized patients will be included in the analysis and analyzed in the groups to which they were randomized.

**Table 2 table2:** A summary of proposed statistics for outcome analysis.

Outcomes	Method of analysis
Toothbrushing duration	Comparison of the 3 groups using an ANOVA, followed by 2-sample *t* tests (A vs B, B vs C, and A vs C) if any statistical significance is found
Bleeding score	Chi-square test
Plaque scores	Comparison of the 3 groups using an ANOVA, followed by 2-sample *t* tests (A vs B, B vs C, and A vs C) if any statistical significance is found
Number of breakages	Kruskal-Wallis test, followed by Mann-Whitney test (A vs B, B vs C, and A vs C) if any statistical significance is found
Number of missed appointments	Kruskal-Wallis test, followed by Mann-Whitney test (A vs B, B vs C, and A vs C) if any statistical significance is found
Total number of appointments	Kruskal-Wallis test, followed by Mann-Whitney test (A vs B, B vs C, and A vs C) if any statistical significance is found
Treatment duration	Comparison of the 3 groups using an ANOVA, followed by 2-sample *t* tests (A vs B, B vs C, and A vs C) if any statistical significance is found
Enamel demineralization	Chi-square test
App subjective quality	Comparison of the 3 groups and different section of the uMARS form by using the Kruskal-Wallis test.
App engagement	Comparison of the 3 groups using an ANOVA, followed by 2-sample *t* tests (A vs B, B vs C, and A vs C) if any statistical significance is found

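### Two primary outcomes, an open visit and no success rule leave the single primary hypothesis without both the stated 5% error and 80% power

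*Protocol article*

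**What the plan says.** All references are to the protocol article; no SAP is shown.

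- **Aims** gives one primary hypothesis: "Using the full functionality of the My Braces app improves adherence to oral hygiene advice in patients undertaking fixed brace treatment". It names no outcome, comparator or time point.
- **Phase 2, Data Collection**: "Two primary outcome measures have been selected, a health behavior outcome and a clinical outcome, as both are felt to be important". These are timed toothbrush use and gingival bleeding. The same section says "A complete data set will be collected at baseline, 3 months into treatment, 12 months into treatment, and at the end of treatment".
- **Table 1** schedules bleeding at baseline and all three later visits. It has no row for brushing time, which **Timed Toothbrush Use** (outcome assessment) defines as an average over sessions stored in the app, with no window.
- **Sample Size**: "The significance level is *P*<.05 with 80% power", assuming ANOVA followed by three pairwise t tests. The brushing-time paragraph reads "accounting for multiple testing, 29 patients are required in each group (n=87" and does not say which tests were counted. The bleeding paragraph follows the same assumptions and gives 38 per group, or 46 with dropout.
- **Planned Analyses** says that factors with P<.05 in the multivariable model "will be considered as having a significant effect on toothbrushing time or gingival bleeding". Table 2 lists ANOVA and t tests for brushing time and a chi-square test for bleeding, with no adjusted level for either.

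**The concern.** A hypothesis stated once but testable on two outcomes, at more than one time, has an error rate and a power only after two choices are made: which visit decides, and whether one outcome is enough. The protocol makes neither choice, yet states 5% and 80%. A team that follows it can support the primary hypothesis from whichever outcome and visit reaches P<.05. If it instead asks for both outcomes, it has less power than it planned for. At stake is whether a positive result can be taken as confirmatory.

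**Working it through.** **1. Which multiplicity is already covered.** Per-group n = 2(z₁₋α/₂ + 0.8416)² / d², with d = 0.85 (20 s / 23.6 s) and d = 0.75 (15 / 20), both from the protocol.

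| α | Brushing time | Bleeding |
|---|---|---|
| 0.05 | 22 | 28 |
| 0.025 | 27 | 34 |
| 0.05/3 | 28.98 → **29** | 37.22 → **38** |
| 0.05/6 | 34 | 44 |

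Only 0.05/3 reproduces both stated figures. The adjustment is therefore for three arm pairs within one outcome, and nothing is left for two outcomes or several visits.

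**2. Error if either outcome suffices.** With independent tests at .05, two tests give 1 − 0.95² = 9.75% and six give 1 − 0.95⁶ = 26.5%. Real tests are correlated, and the protocol gives no correlations. I assumed 0 to 0.5 between outcomes and 0.3 to 0.7 between visits, and simulated three equal arms with 38 per arm. The event counted is a false C versus A finding on at least one test.

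| Reading of the plan | Two outcomes, one visit | Two outcomes, three visits |
|---|---|---|
| C vs A coefficient at .05, no gate (regression route) | 9-10% | about 20-25% |
| C vs A t test at .05 after a significant ANOVA | about 4-5% | 11-14% |
| C vs A at 0.0167 | about 3% | 7-9% |

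The gated 4-5% applies when all three arms are equal. Behind the gate, and at 0.0167, the excess comes from the open visit. Without the gate, two outcomes at one visit already exceed 5%.

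**3. Power if both outcomes are required.** Power per outcome = Φ(d√(n/2) − z₁₋α/₂), with z = 2.394 at 0.05/3 and d = 0.847 (20/23.6) for brushing time.

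- At 38 analysed, √19 = 4.359. Bleeding: 0.75 × 4.359 − 2.394 = 0.875, so 80.9%. Brushing time: 0.847 × 4.359 − 2.394 = 1.30, so 90.3%. Joint power is 0.809 × 0.903 = 73.1% if independent, 76.1% at correlation 0.5 and 78.8% at 0.8.
- With 46 recruited and 20% lost, 46 × 0.8 = 36.8 remain. At 36, the figures are 78.5% and 88.5%. Joint power is 69.5% if independent, 73.0% at 0.5 and 76.1% at 0.8.

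The range is about 70-79%, below 80% throughout. If either outcome suffices, power at 38 is 92-98%, so low power belongs to the both-required rule only.

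**4. What the planned size supports once the test is defined.** Two-sample t test, 36.8 per group, C versus A:

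- α = 0.025: bleeding 82.1%, brushing time about 91%.
- α = 0.05/3: bleeding 77.6%.
- α = 0.05 on each outcome, both required: bleeding 88.8%, brushing time 94.8%. Joint power is 0.888 × 0.948 = 84% if independent.

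**The case against.** Several points on the other side are sound and limit the finding.

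- **Excess error and low power do not occur together.** They belong to different success rules. At a fixed visit, the either-outcome rule has ample power and the both-outcomes rule controls error.
- **A reader might take 20-26% as the error rate of the plan as a whole.** That is the chance that any of six three-arm ANOVAs is significant. The hypothesis concerns group C, and the ANOVA route requires a following t test, which gives 11-14%. The figure of about 20-25% for C versus A applies only to the ungated regression reading.
- **Six tests is one reading.** Because brushing time is an app average, one brushing test plus three bleeding visits is equally fair. Four tests give about 8-9% behind the gate and 5-6% at 0.0167.
- **The significance sentence in Planned Analyses is about model factors.** It is not an either/or rule for trial success. It does fix the level at .05 for each outcome.
- **A reader might set the 20% dropout against the Introduction's** "One multicenter study found that 43% of patients failed to complete treatment". That is non-completion of treatment in another study, not loss of data here, and end of treatment is not named as deciding. The documents do not show a conflict.
- **A reader might infer that correcting over three arm pairs is an error**, because Recruitment explains group B by what it adds "if a difference is found between Groups A and C". That passage justifies including the arm; it sets no test order. Correcting for three planned pairs is legitimate.
- **A hierarchy is often left to the SAP.** True, but this protocol itself fixes the dual primary, the .05 level and a sample size, and that size has a meaning only for a defined visit and success rule.

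**Conclusion.** The point holds in this form. One hypothesis rests on two primary outcomes, with bleeding measured at three later visits, the brushing-time window unfixed, and no deciding visit or success rule. The multiplicity allowance covers arm pairs within one outcome only, and the analysis section carries no adjusted level. With the visit open, neither success rule gives both 5% and 80% at the level used for sizing. If either outcome suffices, the chance of a false C versus A claim over six tests runs from 7-9% (at 0.0167) through 11-14% (ANOVA gate) to about 20-25% (ungated). If both are required, joint power is about 70-79%.

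The arithmetic of step 1 is firm, with a two-sided test assumed because sidedness is not stated. The error and joint-power ranges depend on assumed correlations, and the error figures on all three arms being equal.

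**What to change.** Before recruitment, amend Phase 2 Data Collection, Sample Size and Planned Analyses as follows.

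1. Name one deciding visit and a brushing-time averaging window that matches it; make the other visits secondary. Twelve months is one option. The protocol gives no visit-specific loss, so the 20% should be justified for the visit chosen. If 12 months is chosen, note that the sample size recalculation on 3-month data uses a different visit.
2. State whether one or both primary outcomes must succeed.
3. Make C versus A the first test for each primary outcome, with C versus B tested only if it is significant.
4. If either outcome suffices, control 5% across the two by a 2.5%/2.5% split, Holm or a fixed order. The split is simplest, since step 3 then runs within each outcome at 2.5%; under Holm or a fixed order, the place of C versus B must be written out. If both are required, each can be tested at 5% without a split.
5. Name one primary analysis per outcome. For bleeding, use a mean-difference analysis that matches its sizing in place of the chi-square test.

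The cost is wording. The planned 138 patients give 82% power for bleeding and 91% for brushing time at 2.5%. The downside is that A versus B and the results at the other visits become supportive.
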